### Data analysis

Initial analyses will compare the frequency of baseline levels of outcome and other key variables (e.g., demographic and disease characteristics) for the intervention and usual care groups using a simple chi-square test for categorical variables and a *t*-test for continuous variables with an approximately normal frequency distribution (with transformation if necessary).

Evaluation of intervention effectiveness will be by intention-to-treat using the above statistical tests. Evidence of effect modification by chronic condition diagnoses will be tested statistically. ANOVA and logistic regression for multivariate analyses will be used to adjust for significant differences identified at baseline between intervention and usual care groups in the outcome analyses. Sensitivity analyses will be performed to estimate the effects of missing data using different assumptions (e.g., imputed values). Additional analyses will be conducted to look for evidence of effect modification by pre-specified subgroups: baseline HbA1c (<9 versus ≥9), SBP (<160 versus ≥160), LDL (< versus ≥ median), language (English primary versus English not primary), and age (<versus ≥ median).

Additionally, a cost analysis of the health coaching intervention will examine utilization data and develop predictive models of cardiovascular events prevented and cost savings. The CORE Diabetes model is a computer model used to determine the long-term health outcomes and economic consequences of interventions in either type 1 or type 2 diabetes mellitus. The model projects outcomes for populations by taking into account (a) baseline cohort characteristics and past history of complications; (b) progression of risk factors and transition probabilities between health states based on published sources; (c) effectiveness of treatments such as current and future diabetes management and concomitant medications, screening strategies, and changes in physiological parameters over time; and (d) direct and indirect costs, discount rates, and quality-of-life data to perform economic analysis. The CORE model calculates development of complications, life expectancy, quality-adjusted life expectancy and total costs within populations.

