#### Patient-reported

Surveys at baseline and 12 months examine knowledge of cardiovascular health, chronic disease self-efficacy
[37], patient assessment of chronic illness care (PACIC)
[38], trust-in-physician
[39,40], medication adherence
[41,42], proactive behaviors within the medication visit (e.g., asking questions) as measured by an adapted version of the Perceived Efficacy in Patient-Physician Interactions scale (PEPPI)
[43], depressive symptoms (PHQ8)
[44], the 4-item (short) version of the diabetes distress scale
[45,46], physical activity
[47-49], visits to the emergency room and hospital, health literacy
[50,51], and demographic information. RAs also collect information about prescription medications. At 12 months, patients with a health coach also are queried about interactions with their health coach
[38,52,53].

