#### Utilization of services

The study team is collecting utilization data on clinician, nurse, and nutritionist visits; pharmacy data; and San Francisco Health Plan and SF Department of Public Health Healthy San Francisco claims data on pharmacy medications, emergency room visits and hospitalizations.

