### Outcomes

The goal for each of the 3 conditions are defined at 12 month follow-up as: (1) for patients with enrolled with uncontrolled diabetes, a reduction in HbA1c of at least 1.0% from enrollment; (2) for patients enrolled with uncontrolled hypertension, SBP <140 mm Hg (if non-diabetic) or <130 if diabetic; or (3) for patients with uncontrolled hyperlipidemia, LDL <130 mg/dl if non-diabetic or <100 mg/dl if diabetic.

The primary outcome is the proportion of patients in each arm reaching at least one of the above goals. Secondary outcomes are (1) the proportion of patients in each arm meeting each of the goals separately; and (2) the proportion of patients in each arm meeting the composite and separate goals regardless of their level of control at baseline. We will also compare study arms with respect to changes in self-efficacy for chronic disease management, self-care activities, medication adherence, quality of life, depressive symptoms, satisfaction with chronic illness care and health coaching, communication with physician, bed days, emergency room visits and hospitalizations.

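### Comparing emergency visits, hospitalizations and bed days as changes from baseline is valid but inefficient; adjusting the 12-month count for the baseline count would recover the lost power (minor).

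*Protocol article*

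**What the plan says.** Three statements in the protocol article combine.

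- **Outcomes.** After the primary and the numbered secondary outcomes, a closing sentence begins "We will also compare study arms with respect to changes in self-efficacy for chronic disease management" and ends its list with "communication with physician, bed days, emergency room visits and hospitalizations". Read as written, the three utilization measures are compared as changes.
- **Data analysis, tests.** Chi-square is named for categorical variables and a t-test for roughly normal continuous ones, "with transformation if necessary". Then: "Evaluation of intervention effectiveness will be by intention-to-treat using the above statistical tests".
- **Data analysis, adjustment.** "ANOVA and logistic regression for multivariate analyses will be used to adjust for significant differences identified at baseline". Adjustment therefore depends on a baseline difference being significant. No rule applies to the baseline value of the outcome itself.

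The baseline information exists. The surveys at baseline and 12 months ask about "visits to the emergency room and hospital, health literacy", and the Utilization of services section adds "claims data on pharmacy medications, emergency room visits and hospitalizations". Bed days are not defined, and the list of survey items does not name them.

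**The concern.** A change score gives the baseline count a weight of exactly one. That is close to right only when baseline and follow-up are almost perfectly correlated. For sparse event counts in consecutive years the correlation is usually well below that, so subtraction adds the noise of the first year to that of the second. Conditional adjustment does not repair this, because in a randomized trial the baseline counts will usually not differ significantly.

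What is at stake is precision on three secondary-tier comparisons that describe the use of services. A real reduction in emergency visits or admissions would be missed more often than the collected data require.

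**Working it through.** **The plan's own figure.** The article gives no power, event rate, variance or baseline correlation for utilization. Its one calculation concerns the composite clinical goal: 25% against 40%, two-sided 0.05, power 0.80, 200 per arm. Recalculated: n = [1.96·√(2·0.325·0.675) + 0.8416·√(0.25·0.75 + 0.40·0.60)]² / 0.15² = 1.8485² / 0.0225 ≈ 152 per arm; 200 per arm gives 89.6%. The stated 200 does not reproduce at 0.80, but it errs on the safe side and has no bearing here. I use only the 200 per arm.

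**Why subtraction costs power.** With equal variance σ² and correlation ρ between the two counts:

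- variance of the change: 2σ²(1 − ρ)
- variance of follow-up alone: σ²
- residual variance after adjusting for baseline: σ²(1 − ρ²)

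The efficiency of change relative to adjustment is (1 − ρ²) / [2(1 − ρ)] = (1 + ρ)/2. At ρ = 0.16 this is 0.58, and at ρ = 0.63 it is 0.815. Below ρ = 0.5 the change score is noisier than ignoring baseline altogether.

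**Simulation.** Assumed inputs, none from the article: gamma-Poisson counts with correlated patient effects, rate ratio 0.6, 200 per arm, 1000 trials per scenario (Monte Carlo standard error at most √(0.25/1000) = 1.6 points). Power in %:

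| Control mean per year | Zeros | ρ of counts | t on change | t on 12-month count | ANCOVA | Adjusted negative binomial |
|---|---|---|---|---|---|---|
| ER 0.3 | 79% | 0.11 | 27.3 | 53.3 | 52.9 | 53.4 |
| ER 0.3 | 79% | 0.33 | 36.4 | 53.3 | 55.8 | 54.2 |
| ER 0.6 | 66% | 0.16 | 42.4 | 71.6 | 71.9 | 73.3 |
| ER 0.6 | 67% | 0.49 | 54.1 | 67.6 | 78.1 | 74.4 |
| ER 0.6, more dispersed | 71% | 0.22 | 30.3 | 52.9 | 53.9 | 55.2 |
| ER 0.6, more dispersed | 73% | 0.63 | 52.7 | 52.6 | 72.1 | 70.1 |
| Hospitalizations 0.15 | 88% | 0.09 | 17.0 | 31.7 | 31.9 | 32.1 |
| Hospitalizations 0.15 | 88% | 0.28 | 20.9 | 30.5 | 33.1 | 32.5 |

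Change against ANCOVA loses from 33.1 − 20.9 = 12 to 71.9 − 42.4 = 30 points. ANCOVA, also a normal-theory method, stays within about 4 points of the count model. At low correlation a plain t-test on the 12-month count is within about 2 points. So the change score drives the loss. Using log(x+1) before subtracting recovers only 0 to 4 points for these two outcomes. With no true effect, the t-test on change rejected in 3.7% to 5.5% of trials (bed days included).

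**Hand check of the third row.** Negative binomial variance is μ + 2μ² (dispersion 2), and the patient effects correlate at 0.3. Control: mean 0.6, variance 0.6 + 2·0.36 = 1.32, covariance with baseline 0.3·0.72 = 0.216. Coached, at 12 months: mean 0.36, variance 0.36 + 2·0.1296 = 0.6192, covariance 0.6·0.216 = 0.1296.

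- Change: variances 1.32 + 1.32 − 0.432 = 2.208 and 1.32 + 0.6192 − 0.2592 = 1.680. SE = √(3.888/200) = 0.1394; z = 0.24/0.1394 = 1.72; power Φ(1.72 − 1.96) = 41%.
- ANCOVA: pooled slope (0.216 + 0.1296)/(2·1.32) = 0.131; residual variances 1.286 and 0.608. SE = √(1.894/200) = 0.0973; z = 2.47; power Φ(2.47 − 1.96) = 69%.

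The simulated values were 42.4% and 71.9%.

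**Robust Poisson.** Two further sets of simulations with means from 0.15 to 1 compared the t-test on change with baseline-adjusted Poisson regression with robust errors. The losses were 12 to 25 and 13 to 33 points. Type I error of the robust Poisson in the first set was 4.7% to 6.1%.

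**Bed days** (assumed mean 2, heavy dispersion, rate ratio 0.5). The t-test on change had 39.1% and 86.3% power at ρ = 0.29 and 0.85; ANCOVA had 69.2% and 98.6%. Type I error was 4.5% to 5.6% for ANCOVA, 7.3% and 8.6% for negative binomial, and 9.0% and 23.5% for quasi-Poisson.

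**The case against.** The strongest reply is that this is a condensed article, and that the exact model for additional outcomes is usually left to an analysis plan. The t-test is reserved for roughly normal variables, so zero-heavy counts might fall outside it. The word for change may also be loose: the same list includes satisfaction with health coaching, yet questions about the coach are put only to coached patients and only at 12 months, so no change can exist for that item.

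Part of this stands. The wording may not have been meant strictly for every item, and if the 12-month counts were compared directly, much of the loss would disappear at low correlation. But the article does state both the quantity compared and the family of tests, makes no exception for utilization, and limits adjustment to significant differences. An analysis plan that did better would have to depart from this text.

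A reader might infer more than the document supports:

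- *That the tests are invalid for zero-heavy counts.* Type I error holds at 200 per arm.
- *That chi-square and t-tests are the only methods.* Transformation, ANOVA and logistic regression are also named, though the two models serve only conditional adjustment.
- *That the cost analysis is deprived of a usable input.* The article never says its cost model needs a rate ratio, and a mean difference can be used.
- *That any count model is better.* Model-based negative binomial exceeded nominal error for heavily dispersed bed days.

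**Conclusion.** The point holds as a matter of efficiency. Comparing changes in the utilization counts, with adjustment only when baseline differs significantly, costs roughly 10 to 30 points of power against routine adjustment for the baseline count. The size rests on assumed event rates, dispersion, baseline correlation and a rate ratio of 0.6. Its direction does not depend on them: (1 + ρ)/2 is below one for any correlation short of perfect. The comparison as planned is unbiased and keeps its error rate. Severity is minor, because the outcomes are additional and the trial was sized for the composite goal alone.

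**What to change.** For emergency room visits and hospitalizations, state that the 12-month count is compared between arms with the baseline count as a covariate in every case, whether or not the arms differ at baseline. Use Poisson regression with robust standard errors and report the rate ratio with its 95% CI, or ANCOVA with robust errors and report the mean difference with its 95% CI. Avoid model-based negative binomial regression. Treat bed days the same way if a baseline value is collected, and define the measure; if the counts prove very dispersed, ANCOVA is the safer choice of the two.

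The cost is a sentence of wording and slightly more analysis work. No new data are needed for emergency visits and hospitalizations. The small downside is that the Poisson result is on a ratio scale, which is less direct than a difference in mean visits.

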#### Clinical measures

Hemoglobin A1C, blood pressure, lipids, weight and height are collected at baseline and at 12 months. For diabetic patients, hemoglobin A1c is measured using the DCA Vantage point-of-care testing system. Lipid panels (including calculated LDL) are measured by the clinical laboratory at Clinic A using a Pentra 400 system and through the CardioChek point-of-care testing system at Clinic B. The same method of measurement is used at baseline and at 12 months for each patient. Blood pressure is measured twice, at least two minutes apart, using a calibrated Omron Home Blood Pressure Monitor Model 711-AC on the left arm after the patient has been sitting for at least five minutes. Blood pressure is entered as the average of the two readings unless the two systolic readings differ by more than five points, in which case a third blood pressure reading is taken and the average of all three readings is used. Height is measured using a tape measure and right angle, and weight is measured using a calibrated portable scale.

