### Sample size calculation

Sample size and power calculations were performed for the main outcome of interest: the proportion of patients in each arm who achieve a composite goal of 1) decrease of HbA1C by 1% or more; 2) reaching defined blood pressure goal; or 3) reaching defined LDL goal. Based on a review of the literature and examination of data from a similar clinic (the Family Health Center at San Francisco General Hospital) the study team conservatively estimated the proportion of participants achieving the primary outcome to be 25% in the usual care arm and 40% in the coaching arm for an estimated effect size of 15%. To detect this difference, we needed 200 subjects in each arm to achieve a power of .80 using the standard threshold for a significant difference of .05 (2-sided). To account for a 10% loss to follow-up, the total sample size was calculated at 440 patients.

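### Covariates for the adjusted analysis are chosen by baseline significance tests, and neither the unadjusted nor the adjusted result is named as primary; the cost is precision and pre-specification, not validity

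*Protocol article*

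**What the plan says.** The Data analysis section of the protocol article has three steps.

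1. It starts with tests between the arms at baseline: "Initial analyses will compare the frequency of baseline levels of outcome and other key variables (e.g., demographic and disease characteristics" and so on, "using a simple chi-square test for categorical variables and a *t*-test for continuous variables with an approximately normal frequency distribution". The list of variables is open-ended.
2. It carries the same tests over to the outcomes: "Evaluation of intervention effectiveness will be by intention-to-treat using the above statistical tests". These tests take no covariates.
3. It brings in regression under one condition only: "ANOVA and logistic regression for multivariate analyses will be used to adjust for significant differences identified at baseline between intervention and usual care groups".

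No covariate is named for adjustment. Baseline HbA1c, SBP, LDL, language and age are named, but as subgroup factors for effect modification.

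The Outcomes section defines a binary composite: "The primary outcome is the proportion of patients in each arm reaching at least one of the above goals". Diabetes status sets the SBP and LDL goals, and the HbA1c goal is a fall from the enrolment value. Patient-reported measures are compared as changes. The Clinical measures section confirms that baseline values are available: "Hemoglobin A1C, blood pressure, lipids, weight and height are collected at baseline and at 12 months".

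**The concern.** Unless allocation failed, a significant baseline difference between randomized arms is a chance event. A rule that adjusts only for such differences picks covariates because they happen to be imbalanced. Whether they predict the outcome plays no part.

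Several variables on file should predict the composite from its definition alone:

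- **Diabetes status** moves the SBP and LDL goals.
- **The number of qualifying conditions** sets how many chances a patient has to reach at least one goal. The footnote to Table 2 gives 158 + 229 + 192 = 579 qualifying conditions among 441 patients, or 579/441 = 1.31 each, so the number varies between patients.
- **Clinic** goes with differences in population, team structure and lipid assay.

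Under the stated rule, none of these enters the model unless chance imbalance puts it there. The adjusted model cannot be written down until the baseline tests have been run, and the text leaves two candidate results for the same outcome.

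**Working it through.** **The plan's own figure.** The Sample size calculation section assumes "25% in the usual care arm and 40% in the coaching arm for an estimated effect size of 15" percentage points, and says "we needed 200 subjects in each arm to achieve a power of .80 using the standard threshold for a significant difference of .05 (2-sided". With p1 = 0.25, p2 = 0.40 and mean 0.325:

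n = [1.96 × √(2 × 0.325 × 0.675) + 0.842 × √(0.25 × 0.75 + 0.40 × 0.60)]² / 0.15² = (1.298 + 0.550)² / 0.0225 ≈ 152 per arm, or 165 with continuity correction.

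The stated 200 does not reproduce at 80% power. At 200 per arm, power is Φ[(0.15 − 1.96 × √(0.43875/200)) / √(0.4275/200)] = Φ(1.26) ≈ 0.90 (0.875 with continuity correction). The unadjusted composite test therefore has slack.

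**How often the rule fires.** The level of the baseline tests is not stated; 0.05 is assumed. Any one variable is flagged with probability 0.05, whatever its prognostic value. If k independent variables are tested, the chance of at least one flag is 1 − 0.95^k. The number tested is not given, so k is an assumption:

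| k | 10 | 15 | 20 | 30 |
|---|---|---|---|---|
| at least one flagged | 40% | 54% | 64% | 79% |

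These figures would differ for correlated variables. The 5% for any one variable would not.

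**Continuous outcomes.** Let r be the correlation between baseline and 12 months (assumed; the document gives none), with equal variances at the two times. The variance of ANCOVA is (1 − r²) times that of a t-test on the 12-month value, and (1 − r²)/[2(1 − r)] = (1 + r)/2 times that of a t-test on change.

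| r | ratio to change | reduction | ratio to 12-month value | reduction |
|---|---|---|---|---|
| 0.3 | 0.65 | 35% | 0.91 | 9% |
| 0.5 | 0.75 | 25% | 0.75 | 25% |
| 0.7 | 0.85 | 15% | 0.51 | 49% |

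Change is the more relevant comparator, because the Outcomes section compares changes in the patient-reported measures.

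**Composite.** A simulation used 4,000 trials per setting, 200 per arm, and event rates of 25% and 40% (32.5% in both arms under the null). It had 15 independent baseline variables, one of them prognostic, with an assumed odds ratio per SD of 1.65, 2.7 or 4.5.

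| | OR 1.65 | OR 2.7 | OR 4.5 |
|---|---|---|---|
| Power, unadjusted | 0.900 | 0.893 | 0.897 |
| Power, prognostic covariate fixed in advance | 0.910 | 0.938 | 0.964 |
| Power, covariates chosen by baseline p < 0.05 | 0.896 | 0.895 | 0.906 |
| Type I error, unadjusted | 0.046 | 0.052 | 0.055 |
| Type I error, chosen by baseline p < 0.05 | 0.044 | 0.045 | 0.050 |
| Type I error, either of these two significant | 0.050 | 0.054 | 0.060 |
| Prognostic covariate selected (25% vs 40% runs) | 4.7% | 4.8% | 5.6% |

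The gain from fixing the covariate is 0.910 − 0.900 = 1.0, 0.938 − 0.893 = 4.5 and 0.964 − 0.897 = 6.7 power points. The Monte Carlo standard error of one power figure is √(0.9 × 0.1/4000) ≈ 0.005, so the gain at the weakest covariate is small against simulation noise. The significance rule recovers almost none of the gain.

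**The case against.** The other side has much that stands.

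- **Validity.** A reader might infer that the rule biases the result or inflates type I error. The documents do not support this. The intention-to-treat chi-square is valid by design. The rule looks at baseline data, not 12-month results. Even reporting whichever of the two results is significant gave at most about 0.06.
- **Use of baseline values.** A reader might infer that they are thrown away. They are not: they enter the HbA1c goal, the change scores, the screen for adjustment and the subgroups. The accurate statement is that none is fixed in advance as a covariate.
- **Power.** A reader might infer that the trial is underpowered as a result. At 200 per arm the unadjusted test has about 0.90 power for the assumed difference, against a stated 0.80.
- **Assumptions.** The correlations, covariate strengths and number of variables tested are not in the document, and it gives no data on how strongly the number of qualifying conditions predicts success. This stands, which is why ranges are shown.
- **A condensed article.** A full covariate list may be left to an analysis plan, so its absence is no finding. This does not answer the point, because the article states a selection rule, and that rule is what is criticised.
- **Order of the text.** The unadjusted tests come first, which suggests that they lead. But the regression sentence also concerns the outcome analyses, and neither result is labelled primary.

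**Conclusion.** The point holds as one of efficiency and pre-specification, and the text should be changed. The stated rule selects on chance imbalance, so a given strong predictor is left out in about 95% of trials if baseline tests are run at 0.05. It also leaves open which of two results is primary.

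The precision given up is moderate to large for continuous outcomes under the assumed correlations. For the composite it is small to moderate and depends wholly on the assumed covariate strength. Nothing here undermines the unadjusted intention-to-treat comparison.

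**What to change.** Delete the baseline-significance rule, and name one primary analysis whose covariates are fixed before outcome data are analysed.

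- **Composite:** logistic regression on arm, clinic, diabetes status and an indicator for each qualifying condition (HbA1c, SBP, LDL), reported as a standardized risk difference, with the unadjusted chi-square as supportive. At the planned rates, 400 evaluable patients × 0.325 = 130 events for six model terms.
- **Continuous outcomes:** ANCOVA of the 12-month value on arm, its baseline value and clinic.
- **Baseline table:** descriptive, without p-values.

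The cost is wording only, since every covariate is already collected. The downside is that the main estimate comes from a model rather than a 2×2 table; keeping the chi-square as support lets readers see the simple comparison.

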**Clinical characteristics**		
Body mass index (BMI)		31.4 ± 6.8
Hemoglobin A1c^**^		9.9 ± 1.5
Low-density lipoprotein (LDL)^**^		146.7 ± 34.7
Systolic blood pressure^**^		159.4 ± 15.4

* For the 328 participants born outside the United States.

**Includes only patients qualifying for the study on this measure (n = 158 for hemoglobin A1c, 229 for LDL, and 192 for systolic blood pressure).

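### The planned effect-modification analyses are specified only as two-group splits of baseline HbA1c, SBP, LDL and age; if modification is roughly linear, this loses about a third to three fifths of the information

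*Protocol article*

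**What the plan says.** The Data analysis section announces the work this way: "Additional analyses will be conducted to look for evidence of effect modification by pre-specified subgroups". It then lists the subgroups: "baseline HbA1c (<9 versus ≥9), SBP (<160 versus ≥160), LDL (< versus ≥ median"), primary language (English or not), and "age (<versus ≥ median"). Language is categorical. The other four are continuous measurements reduced to two groups. No value is given for the LDL and age medians, no reason for the cuts at 9 and 160, and no version with the variables kept continuous.

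Table 2 reports these variables as means and SDs, so the trial holds them in continuous form. HbA1c, LDL and SBP are summarised only for patients who qualified on that measure ("n = 158 for hemoglobin A1c, 229 for LDL, and 192 for systolic blood pressure").

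The Sample size calculation section covers only the overall composite, assuming "25% in the usual care arm and 40% in the coaching arm". It gives no power for any interaction.

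**The concern.** Whether coaching helps more in patients further from goal is a question the protocol sets itself. A two-group split treats everyone on one side of the cut as alike. HbA1c entry is at 8.0% and the mean among qualifiers is 9.9, so a cut at 9 separates the 8.0–8.9 band from everyone else. Any gradient above 9 is invisible to that comparison.

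Interaction tests in a trial sized for a main effect are weak to begin with. A further loss of information makes a null result more likely, and a null result could be misread as evidence that coaching works equally well at all levels of baseline control.

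**Working it through.** **The plan's own figure.** There is none for effect modification. The only stated calculation is for the composite: "we needed 200 subjects in each arm to achieve a power of .80", with the "standard threshold for a significant difference of .05 (2-sided"). The standard two-proportion formula for 25% versus 40% gives 152 per arm (165 with continuity correction), and 200 per arm gives 89.6% power, so the stated pairing does not reproduce. That is a separate matter. It means only that the subgroup tests are weak even at a sample size that is generous for the main effect.

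**Inputs.** Cuts from Data analysis. Mean ± SD from Table 2: HbA1c 9.9 ± 1.5, SBP 159.4 ± 15.4, LDL 146.7 ± 34.7 (qualifiers only), age 52.7 ± 11.1. Entry thresholds from Identification and recruitment: HbA1c 8.0, SBP 140, LDL 100 if diabetic (160 if not).

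**Information retained under a linear modifier.** This is the squared correlation between X and the indicator that X is at or above the cut c. Let p = P(X < c).

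- Normal shape: retained = φ(z)² / [p(1 − p)], with z = (c − mean)/SD.
  - At the median: 0.3989² / 0.25 = 0.637.
  - SBP: z = 0.6/15.4 = 0.039; 0.3986² / (0.5155 × 0.4845) = 0.636.
  - HbA1c: z = −0.9/1.5 = −0.6; 0.3332² / (0.2743 × 0.7257) = 0.558.
- Gamma shifted to the threshold L: shape k = ((mean − L)/SD)², scale θ = SD²/(mean − L), x = c − L; retained = [θ·x·f(x)]² / [SD²·p(1 − p)].
  - HbA1c: k = 1.604, θ = 1.184, x = 1, f = 0.3665, p = 0.324; 0.434² / (2.25 × 0.324 × 0.676) = 0.383.
  - SBP: k = 1.587, θ = 12.22, x = 20, f = 0.02384, p = 0.620; 5.829² / (237.16 × 0.620 × 0.380) = 0.608.
  - LDL (L = 100): median 138.4; 0.545, by numerical integration.

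| Modifier | Loss, normal | Loss, shifted gamma |
|---|---|---|
| Age, median | 36% | not applicable (34% if truncated to 18–75) |
| SBP, 160 | 36% | 39% |
| LDL, median | 36% | 46% |
| HbA1c, 9 | 44% | 62% |

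A more skewed shifted lognormal gives 48% (SBP), 56% (LDL) and 74% (HbA1c).

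**Power of the split tests.** Suppose the interaction were as large as the whole assumed effect (15 points), around an average effect of 15 points on a 25% control rate. For age with 400 analysed, each half has 100 per arm, with control 25% and coaching 32.5% or 47.5%. The variance is (0.1875 + 0.2194 + 0.1875 + 0.2494)/100 = 0.00844 and the SE is 0.0919. Power = Φ(0.15/0.0919 − 1.96) = 37%. Among qualifiers after 10% loss (158, 192 and 229 become 142, 173 and 206) it is 15% for HbA1c, 18% for SBP and 22% for LDL.

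**Continuous versus split, simulated.** Logistic model, linear modifier, 1,000 runs per setting, normal age and shifted-gamma clinical measures:

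| Modifier (N) | Slope 0.3 per SD: continuous / split | Slope 0.5 per SD: continuous / split |
|---|---|---|
| Age (400) | 29% / 20% | 59% / 44% |
| HbA1c (142) | 10% / 7% | 26% / 11% |
| SBP (173) | 12% / 11% | 31% / 22% |
| LDL (206) | 17% / 11% | 34% / 20% |

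**When modification is not linear.** With a true step at the median age, the split has 45% power and the linear term 31%. With the gamma HbA1c distribution and modification that rises and then levels off, efficiency (split versus linear) is 83% versus 47% for a plateau at 9.5, 77% versus 60% at 10, 68% versus 70% at 10.5, and 61% versus 78% at 11.

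**The case against.** The strongest reply has four parts.

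- **A condensed article.** One sentence names subgroups and no model, and an unseen analysis plan may add continuous interactions. That is fair as far as it goes. But the cut-points are written down and called pre-specified, so the split is a stated choice, and the point is about that choice.
- **Linearity is assumed.** This stands, and it limits the claim. A reader might infer that the splits throw away 35% to 60% of the information whatever the truth. The documents do not support that: they give no shape for the modification, and the outcome is attainment of at least one goal, so a constant slope over the whole range is not guaranteed. They do not support a step at 9 or 160 either.
- **Who is analysed.** A reader might also infer that the HbA1c test is worth only about 60 patients (158 × 0.38). That needs both the gamma shape and restriction to the 158 qualifiers. Data analysis does not say who enters each subgroup test, HbA1c is measured in diabetic patients generally, and a secondary outcome covers patients regardless of baseline control. LDL qualifiers also mix two entry thresholds, so an LDL interaction, split or continuous, is partly a diabetes interaction.
- **The median cuts.** They might look like data-driven choices. A median of a baseline covariate uses neither outcome nor arm, and recruitment was complete, so it offers no room to pick a cut by result.

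It is also true that the gain is limited, because the continuous tests remain modest in power.

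**Conclusion.** The point holds as a minor, inexpensive improvement. Four continuous modifiers are specified only as two-group splits. Under a roughly linear modifier the loss is about 36% for age, 36–39% for SBP, 36–46% for LDL and 44–62% for HbA1c. The last three figures apply to qualifiers, with normal to shifted-gamma shapes assumed from means and SDs alone. HbA1c is the worst case because its cut lies well below the mean. If modification steps or plateaus near the cut, the loss is smaller or reversed.

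The primary comparison and its sample size are untouched. No outcome data are shown, so nothing here says that any subgroup conclusion would change.

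**What to change.** Before outcomes are examined by arm, state that the formal test of effect modification by baseline HbA1c, SBP, LDL and age is the arm-by-continuous-baseline interaction. Pre-specify a low-degree-of-freedom spline for each as a check on non-linearity, which also covers a plateau. Say whether each test uses all patients with the measurement or only those who qualified on it. Keep the two-group estimates at the planned cuts, with confidence intervals, for display. Language stays as planned.

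The cost is a few lines of plan and code, with no new data. Some power is lost if the effect truly steps at a cut. The tests remain exploratory and modest in power, and should be reported as such.
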